**Cautiousness**	
The degree of cautiousness displayed by an individuals social contact patterns and general precautionary social behavior.	Stuurman et al. (48) mention the number of people living in the individuals household and the presence of a child in the individuals household as indicators for this variable. This information is, however, not available in the BARMER database.
**Health status**	
The general health status of an individual. This includes both physical and psychological wellbeing.	Two indicators will be used as proxies for this variable. We will consider: (1) A modified version of the Charlson comorbidity index (81) that does not include the main diseases of interest in this study, calculated using ICD codes from the last year. (2) The number of inpatient hospital stays in the last 2 years. (3) The current official level of care.

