## 1 Introduction

Individuals with autoimmune diseases, such as multiple sclerosis (MS), chronic inflammatory bowel diseases (IBD), or chronic inflammatory rheumatoid diseases (CIRD) have a highly increased chance of being infected with various vaccine-preventable infectious diseases (1, 2). This increased susceptibility, coupled with a higher chance of worse outcomes, has been shown repeatedly for MS patients (3), IBD patients (4, 5), and CIRD patients (6) compared to the general population and is thought to be the result of the autoimmune disease itself, existing comorbidities and the use of immunosuppressive therapies (5). Influenza and herpes zoster are two such diseases, which may lead to serious complications or even death (7, 8). The primary way to prevent these diseases in the general population is through the use of vaccines. The efficacy and effectiveness of these vaccines is usually determined using large randomized controlled trials, from which individuals with autoimmune diseases are often excluded (9). It is therefore unclear whether the effectiveness of the respective vaccines in individuals with autoimmune diseases is comparable to the effectiveness in individuals without these diseases.

Only a few studies tried to directly estimate the effects of herpes zoster or influenza vaccines in MS, IBD, or CIRD patients. Some single-arm prospective studies have shown an adequate immune response to an influenza vaccination in MS patients, but inconclusive results for pneumococcal vaccination in similar patients (10, 11). A few observational studies, based on routinely collected claims data, have demonstrated that vaccination against herpes zoster may be safe and effective in IBD patients (12–14), but the evidence for CIRD and MS is much more limited (15, 16). A meta-analysis of randomized controlled trials aiming to estimate the safety and effectiveness of the herpes zoster vaccine in both immunocompetent and immunocompromized patients in general also found the vaccine to be effective and safe (17), although it is unclear whether these results hold for MS or CIRD patients specifically.

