## 2 Methods and analysis

### 2.1 Aims and objectives

The primary aim of this study is to estimate the effectiveness of two different kinds of vaccines in individuals with either MS, IBD or CIRD and individuals without these diseases and to compare the effectiveness between these populations. More specifically, we are interested in the effectiveness of two types of vaccines:

Vaccines against herpes zoster (shingles).Vaccines against influenza.

A secondary aim of this study is to investigate the impact of immunosuppressive medication taken before vaccination on vaccine effectiveness in each of the three disease groups. It has been shown that the use of immunosuppressive medication raises the risk of developing infectious diseases (23). Since a large proportion of MS, IBD and CIRD patients receive such medications, disentangling the effect of the actual disease and the medication is crucial to make valid vaccine recommendations (24).

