**Treatment**	
The kind of medical treatment an individual has received in the past and is currently receiving.	A variable that classifies the medical treatment an individual has received in the last year into different categories of severity in regards to immunosuppressive effect. More details are given in the online supplement.

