**Disease status**	
Whether the individual belongs to one or more of the three disease groups considered in this study.	The exact definition of each disease is given in Section 2.5.1.

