**Vaccination plan**	
For individuals with MS, IBD, or CIRD it is not unusual that the vaccination is planned in advance by the physician and aligned with changes in medication that may have immunosuppressive effects. For example, the physician may decide that the individual should be vaccinated next week. To allow the patients immune system to make a proper response to the vaccination, a new prescription of immunosuppressive medication is then delayed for a few weeks. This variable states whether such a plan was made or not.	An indicator of whether a person receives a medication change shortly after vaccination may be created. However, this type of indicator breaks the time-line, since information from the future would be used. We will perform an additional sensitivity analysis to determine the effect of using this indicator as an adjustment variable.

Using this DAG and the *backdoor criterion* (47), we then identified separate sets of factors that we need to adjust for in each vaccine effectiveness analysis (53). These sufficient adjustment sets are very similar. In both of the two considered analyses, we will adjust for *Age, Sex, Place, Calender Time, Cautiousness, Disease Status, Healthcare-Seeking Behavior* (HSB), *Treatment, Health Status*, and *Vaccination Plan*. The only differences are that we additionally have to adjust for *Chicken Pox* and *Herpes Zoster Immunity* in the herpes zoster vaccine effectiveness analysis and that we also have to adjust for *Influenza Immunity* in the influenza vaccine effectiveness analysis.

Note that, given our assumptions, there is no need to adjust for socioeconomic status in either analysis, because we hypothesize that the effect of this variable on each outcome is only indirect and is thus already adjusted for by including the other variables. It is also not strictly necessary to adjust for sex in the influenza vaccine effectiveness analysis for the same reason. We choose to include sex anyway, because it can be seen as a proxy for other relevant confounders such as cautiousness that we may not be able to fully adjust for given the mentioned indicators (48).

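### Activity and severity of MS, IBD or CIRD are measured only indirectly in the adjustment set, so residual confounding confined to the diseased group could bias the primary vaccine-effectiveness ratio in either direction

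*Protocol article*

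**What the plan says.** The Introduction says that the raised infection risk of these patients "is thought to be the result of the autoimmune disease itself, existing comorbidities and the use of immunosuppressive therapies". Section 2.1 adds, for the secondary aim, that "disentangling the effect of the actual disease and the medication is crucial to make valid vaccine recommendations".

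Table 2 and Section 2.5.4 then fix what is adjusted for:

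- **Disease status:** "Whether the individual belongs to one or more of the three disease groups considered in this study". It is matched exactly (Section 2.6.1) and enters the Cox model (Section 2.6.2).
- **Health status:** "A modified version of the Charlson comorbidity index (81) that does not include the main diseases of interest in this study"; "The number of inpatient hospital stays in the last 2 years"; "The current official level of care".
- **Treatment:** the last year's therapy, classed "into different categories of severity in regards to immunosuppressive effect".
- **Healthcare-seeking behaviour:** includes primary care visits and all physician visits in the year before entry.
- **Vaccination plan:** for these patients "it is not unusual that the vaccination is planned in advance by the physician and aligned with changes in medication". This concept belongs to the required adjustment set, but its indicator uses information from after vaccination and appears only in a sensitivity analysis.

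Section 2.6.2 names one interaction, between vaccination and disease status. Table 1 gives the first causal contrast as the ratio of vaccine effectiveness (VE) in the diseased to that in the non-diseased.

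**The concern.** Of the three sources of infection risk in the Introduction, comorbidity and therapy are graded, while the disease itself is only present or absent. A patient in remission and one recently admitted for a flare can match exactly on disease group and have the same Charlson score.

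This matters more here than in a study of a single VE. Activity of the index disease exists only in the diseased, so any confounding it leaves does not cancel in the ratio. For vaccination misclassification, the Discussion argues that the contrast is unbiased if the error rate is equal across disease groups. No such argument is available for a factor that one group cannot have. A ratio away from 1 could then arise without true effect modification, or a true difference could be masked.

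**Working it through.** The article gives no bias figure to reproduce. The check has two parts: what the covariates carry, and how large a residual bias could be.

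**1. What the planned covariates carry**

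| Covariate | Window | Information on index-disease activity |
|---|---|---|
| Disease status | at entry | presence only |
| Modified Charlson index | last year | none, by construction |
| Inpatient stays | 2 years | partial: all causes, recent and old together |
| Level of care | current | partial: disability |
| Physician visits | last year | partial: all causes |
| Treatment class | last year | partial: graded by immunosuppressive effect, not by activity |

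Four rows are therefore partial proxies. None excludes care for the index disease, and none isolates it. With only the vaccination-by-disease interaction named, one further hospital stay has the same coefficient in a patient with Crohn's disease as in a person with none of the three diseases. Section 2.6.6 also concedes a limit of the treatment class: it allows only partial adjustment for corticosteroids.

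**2. Size of a residual bias (illustration)**

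All inputs are assumptions; none is in the article.

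- True VE is equal in both groups, so the true ratio is 1.
- Active disease is present in a0 = 0.20 of diseased controls and in a1 = 0.12 of diseased vaccinees (vaccination put off when active) or a1 = 0.30 (more severe patients vaccinated more).
- The infection risk ratio for active against quiet disease is g = 1.5, 2 or 3.
- The proxies absorb none of the imbalance.

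Formulas:

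- B = [1 + a1(g − 1)] / [1 + a0(g − 1)]
- Observed diseased VE = 1 − (1 − VE) × B
- Ratio = observed diseased VE / VE

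At true VE 0.40:

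| a1 | g | B | Diseased VE | Ratio |
|---|---|---|---|---|
| 0.12 | 1.5 | 1.06/1.10 = 0.964 | 0.422 | 1.05 |
| 0.12 | 2 | 1.12/1.20 = 0.933 | 0.440 | 1.10 |
| 0.12 | 3 | 1.24/1.40 = 0.886 | 0.469 | 1.17 |
| 0.30 | 1.5 | 1.15/1.10 = 1.045 | 0.373 | 0.93 |
| 0.30 | 2 | 1.30/1.20 = 1.083 | 0.350 | 0.875 |
| 0.30 | 3 | 1.60/1.40 = 1.143 | 0.314 | 0.79 |

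**Higher VE.** The formulas combine to ratio = 1 + [(1 − VE)/VE] × (1 − B). The multiplier is 0.60/0.40 = 1.5 at VE 0.40 and 0.30/0.70 = 0.43 at VE 0.70. At VE 0.70 the same inputs give 1.02 to 1.05 (a1 = 0.12) and 0.98 to 0.94 (a1 = 0.30).

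**Partial absorption.** Suppose the proxies remove half the difference in prevalence, with g = 2 and VE 0.40. Then a1 = 0.16 gives B = 1.16/1.20 = 0.967 and a ratio of 1.05; a1 = 0.25 gives B = 1.25/1.20 = 1.042 and a ratio of 0.94.

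**No residual link.** If a1 = a0 after adjustment, or g = 1, then B = 1 and the ratio is 1.

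**The case against.** Much of the case for the plan stands.

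- A reader might infer that disease severity is missing from the adjustment altogether. It is not: treatment class, inpatient stays, level of care and visits all carry part of it. The treatment categories and exact disease definitions are in an online supplement that was not available, so how finely they grade severity cannot be judged.
- A reader might take the reduced Charlson index as an error. It is not one. Disease group is matched exactly, and taking disease presence out of a comorbidity score loses no information on activity.
- The Introduction compares patients with the general population. It does not state that activity within a disease changes infection risk. The Vaccination plan entry ties timing to medication changes, not to flares. That activity drives both vaccination and infection is plausible, but it is an inference.
- Table 1 says the whole analysis is repeated with urinary tract infection as negative control outcome. That repeat includes the disease interaction, so confounding confined to the diseased could show up there. The secondary analysis is also stratified by disease group and medication severity, and residual confounding is conceded in general terms.

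These points lower the likely size of the problem without closing it. The negative control can reveal confounding but does not remove it. The stratified analysis includes only diseased patients, so it does not yield the primary ratio. Where the article names a confounder it cannot measure, it names cautiousness; disease activity is not named.

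**Conclusion.** The point holds in a limited form. Index-disease activity and severity are measured directly by no adjustment variable, and the indirect proxies have, as written, common coefficients across diseased and non-diseased people. Residual confounding from this source would be confined to the diseased and can bias the primary ratio either way.

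A reader might go further and conclude that the ratio will be distorted. The article does not support that. Bias requires activity to remain related to both vaccination and infection after the planned adjustment, and the article gives no figure for either link. With no absorption by the proxies, the illustration gives ratios of 1.05 to 1.17 or 0.93 to 0.79 at VE 0.40, and 0.94 to 1.05 overall at VE 0.70. These show what the assumed imbalances would do and are not estimates of the actual bias. The change is worth making because the direction is unknown and the data needed are already held. It is an improvement to the adjustment set and does not correct an internal contradiction.

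**What to change.** 1. Add pre-baseline, disease-specific indicators to the Cox model used for g-computation and to the entropy-balancing weights: an inpatient stay with the index disease as main diagnosis in the last 90 days, and in the last 12 months, both set to zero in the non-diseased. Section 2.5.3 says inpatient codes carry exact dates. Unlike the Vaccination plan indicator, these use no information from after entry. They overlap with the 2-year stay count but separate cause and recency, which that count cannot do.
2. Let the health-status and visit proxies have disease-specific coefficients, through interactions with disease status.
3. Show covariate balance by vaccination arm within each of MS, IBD and CIRD.
4. State in advance that the urinary tract infection result will be read by disease group, and name disease activity among the possible residual confounders.

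Two further indicators need limits. Incapacity certificates for the index disease apply only to people in work, so they should enter only with an indicator for being in work. Disease duration should enter only as a coarse category: data start in 2013, so in the 2015/16 season observable duration cannot exceed about 2 years 8 months at the start or 3 years 5 months at the end.

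The cost is a few more covariates from existing claims and some loss of precision, most of all in MS, the smallest group (about 50,000 patients, against 80,000 with IBD and 300,000 with CIRD).

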**Treatment**	
The kind of medical treatment an individual has received in the past and is currently receiving.	A variable that classifies the medical treatment an individual has received in the last year into different categories of severity in regards to immunosuppressive effect. More details are given in the online supplement.
**Disease status**	
Whether the individual belongs to one or more of the three disease groups considered in this study.	The exact definition of each disease is given in Section 2.5.1.

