Treatment Assignment	Individual randomization, stratified on disease status (MS, IBD, CIRD or none of these).	To emulate randomization we adjust for multiple confounders using a combination of matching and g-computation.
Start and end of trial	(1) Herpes zoster vaccine effectiveness trial: 01.12.2018–31.12.2021^a^ (2) Influenza vaccine effectiveness trials:*^b^* (a) 01.09.2015–31.05.2016 (b) 01.09.2016–31.05.2017 (c) 01.09.2017–31.05.2018 (d) 01.09.2018–31.05.2019	
Start and end of follow-up	Start of follow-up: time of assignment to treatment strategy. End of follow-up: The earliest of death, loss-to-follow-up or administrative end-of-follow-up (end of the respective study).	
Outcomes	(1) Herpes zoster vaccine effectiveness: medically attended Herpes zoster infection (2) Influenza vaccine effectiveness: (a) medically attended influenza infection (b) severe medically attended influenza infection	
Causal contrast	(1) The ratio between the vaccine effectiveness (1 - the relative risk to develop the outcome at time *t* given the treatment) in the diseased group (individual has either MS, IBD or CIRD) and the non-diseased group (2) The vaccine effectiveness for each of the three disease groups (MS, IBD, CIRD), stratified by the categorized severity of received medication in regards to immunosuppressive effect. Both contrasts will be estimated as *intention-to-treat* and *per-protocol* effects. The target estimand is the average causal effect on the treated (ATT).	
Statistical analysis	Computing formal contrasts of simple Kaplan-Meier estimates.	Time-dependent 1:1 matching by days without replacement. Controls will be matched exactly by age in years, biological sex, place of residence, and disease status. The matched sample will be analyzed using a Cox model with additional adjustment for further confounders. G-computation based on this Cox model and a non-parametric estimate of the baseline hazard will be used to estimate the target estimand. Both *intention-to-treat* and *per-protocol* effects will be estimated by different censoring schemes as described in Section 2.6.3.
Sensitivity analysis	None.	The entire analysis will be repeated using *medically attended urinary tract infection* as a negative control outcome to assess the robustness of the confounder adjustment employed.

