### 2.5 Measures

#### 2.5.1 Disease definitions

We will consider three main types of autoimmune disease groups: MS, CIRD, and IBD. To determine whether an individual has developed one or multiple of the diseases contained in each group at certain points in time using the BARMER data, we developed new algorithms based on previous research. For MS all existing subtypes of the disease are considered. Our algorithm to identify MS is loosely based on the algorithm developed by Culpepper et al. (34). We further define an individual to have CIRD only when that individual either has *rheumatoid arthritis, axial spondyloarthritis* or *systemic lupus erythematosus*. Those three diseases are each identified using different algorithms, based on previous work (35–37). Similarly, we define IBD to be present if the individual has *Crohn's disease* or *colitis ulcerosa*, which are also identified separately using algorithms based on previous research (38, 39). The exact definitions used for each disease and sub-disease are given in the online supplement of this article.

Through the course of the VAC-MAC project, these definitions have already been applied to the BARMER data. We were able to identify approximately 50,000 patients with MS, 300,000 patients with CIRD and 80,000 patients with IBD between the 01.01.2013 and the 31.12.2021. Additionally, approximately 9,000 of these patients had more than one of the three considered disease categories. Although this constitutes a “look into the data” before this study protocol was published, this procedure is in accordance with recommendations by Wang and Schneeweiss (40), who state that performing data checks before study registration actually increase the validity of the study.

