#### 2.6.1 Matching method

Due to the different target trials per vaccine of interest, the planned matching and analysis strategy also differs slightly. To analyze the effectiveness of the herpes zoster vaccine, a single matching process will be used. For the influenza vaccine effectiveness trials we will use the same procedure, with the only difference being that it will be performed separately for each influenza season. The matching will be carried out as follows.

For the previously defined start date of the respective trial, the eligibility of all individuals contained in the BARMER database will be determined using the above mentioned inclusion criteria. Eligibility will be checked using only the information available at that time. Every individual who was vaccinated with the vaccine of interest on this date is subsequently included in the dataset, in the treatment group. For every individual included in this way, we then include *k* further individuals who fulfill the inclusion criteria, but have not been vaccinated yet, in the control group. These controls will be matched exactly by age in years, gender, place of residence and disease group. If more than *k* potential controls are identified for a case, *k* controls will be picked at random from these. We will try to include 2 controls per case first (*k* = 2), but will lower this number to 1 if the number of available matches is insufficient. The date of inclusion equals “time zero” (27) for all individuals. Information about all relevant confounders is recorded as available on this date, corresponding to baseline information. This procedure is repeated on all subsequent days, until the emulated trial is over.

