#### 2.6.2 Analysis method

The matching process described above reduces the time-dependent vaccination variable to a time-fixed binary variable, allowing the use of well known analysis methods. We will first describe the matched data using descriptive statistics, stratified by treatment group and disease status. Means and standard deviations will be calculated for normally distributed continuous variables, median and ranges will be used for non-normally distributed continuous variables and counts and percentages will be calculated for categorical and binary variables. Appropriate statistical tests, such as *t*-tests and chi-squared tests, will be used to formally compare the distribution of these variables at baseline. Histograms and boxplots, stratified by both treatment groups and disease groups will also be drawn. In addition, the number of vaccinated individuals, matched controls and number of potential controls evolving over time will be graphically displayed as recommended by Thomas et al. (56).

For the estimation of the vaccine-effectiveness, we will employ standard time-to-event analysis methods, such as Kaplan-Meier curves and Cox models. No complex marginal structural models or similar strategies are required, because only information before inclusion into the trial is used for adjustment, making it impossible for *treatment-confounder* feedback (32) to occur.

Because we only match by age in years, gender, place of residence and disease status, we still have to adjust for the other confounders mentioned earlier to obtain unbiased estimates of the average causal effect we are interested in. A Cox model using the time to the respective outcome of interest as dependent variable and the treatment variable, the disease status and all relevant confounders (as observed at trial inclusion) as independent variables will be used to perform this adjustment. Since we are interested in the effect-modification of the vaccine effectiveness by disease status, we will also include an interaction term of these two variables in the model. This model, in conjunction with an estimate of the baseline hazard function (60), will then also be used to estimate confounder-adjusted survival curves using g-computation (61). These curves will then be used to derive time-dependent relative risk estimates, which will in turn be used to derive the vaccine effectiveness as (62):

(1)
$$\begin{array}{l} \theta \left(t\right)=1-RR\left(t\right), \end{array}$$

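### CIRD and IBD are matched and adjusted only as broad groups although their five sub-diseases are identified separately, so residual confounding by sub-disease is possible and cheap to address in the outcome model

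*Protocol article*

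**What the plan says.** Section 2.5.1 defines CIRD as any of rheumatoid arthritis, axial spondyloarthritis or systemic lupus erythematosus, and adds: "Those three diseases are each identified using different algorithms, based on previous work". IBD is Crohn's disease or ulcerative colitis, "which are also identified separately using algorithms based on previous research". The same section says that these definitions have already been applied to the data.

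From there on, only the three groups appear:

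- **Confounder (Table 2, Disease status):** "Whether the individual belongs to one or more of the three disease groups considered in this study".
- **Matching (Section 2.6.1):** "These controls will be matched exactly by age in years, gender, place of residence and disease group". Table 1 has the same rule with different wording: "Controls will be matched exactly by age in years, biological sex, place of residence, and disease status".
- **Outcome model (Section 2.6.2):** the Cox model takes "the treatment variable, the disease status and all relevant confounders (as observed at trial inclusion) as independent variables", plus an interaction of vaccination with disease status.
- **Secondary analysis (Section 2.6.2):** stratified by disease group and severity of immunosuppressive medication.
- **Primary contrast (Table 1):** the ratio of VE "in the diseased group (individual has either MS, IBD or CIRD) and the non-diseased group".

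No part of the article matches, adjusts or stratifies by sub-disease, and none gives a reason specific to this choice. Section 2.5.4 says that factors with the same assumed causes were merged in the DAG to keep it readable. That explains the drawing, not the choice of model covariates.

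**The concern.** Within CIRD, and within IBD, the vaccinated and their matched controls may differ in sub-disease mix. If sub-disease is related both to being vaccinated and to being infected, after everything else that is matched or adjusted, the group's relative risk is confounded.

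The other covariates overlap with sub-disease but do not replace it. The Charlson index is modified to leave out the main diseases of interest, so it does not separate them. The treatment variable is a severity category for immunosuppressive effect over one year, and patients with different diseases can fall in the same category. Hospital stays, level of care and healthcare use are indirect.

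At stake are the VE estimates for CIRD and IBD, the ratio against the non-diseased, and the medication-stratified analysis. Section 2.1 wants that last analysis to separate the effect of the disease from that of the medication.

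**Working it through.** The article states no figure on this point, so there is nothing to reproduce. The check has two parts.

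**1. How much of the diseased population belongs to mixed groups.** Section 2.5.1 gives "approximately 50,000 patients with MS, 300,000 patients with CIRD and 80,000 patients with IBD".

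- Total memberships: 50,000 + 300,000 + 80,000 = 430,000.
- CIRD share: 300/430 = 70%.
- CIRD plus IBD: 380/430 = 88%.

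These are memberships, not persons (about 9,000 patients are in more than one group). They cover everyone identified in 2013–2021, not the matched vaccinated patients who define the ATT.

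**2. Possible size of the bias.** For one unadjusted sub-disease with share p1 in the vaccinated, p0 in the controls and risk ratio R for the outcome:

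- B = [1 + p1(R − 1)] / [1 + p0(R − 1)]

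For several sub-diseases:

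- B = Σ(share in vaccinated × relative risk) / Σ(share in controls × relative risk)

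Then observed VE = 1 − (1 − true VE) × B. The VE ratio is observed VE / true VE, taking the true VE as equal in both groups (true ratio 1) and the non-diseased estimate as unbiased.

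All shares and risks below are assumptions; none comes from the article. No credit is taken for immunosuppression category, comorbidity, healthcare use or prior infection.

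- **A:** one sub-disease, p1 = 0.12, p0 = 0.10, R = 1.25. B = 1.030/1.025.
- **B:** one sub-disease, p1 = 0.20, p0 = 0.10, R = 2.0. B = 1.20/1.10.
- **C:** rheumatoid arthritis / axial spondyloarthritis / lupus at 75/18/7% in the vaccinated and 70/25/5% in controls, risks 1/0.7/1.5. B = (0.750 + 0.126 + 0.105)/(0.700 + 0.175 + 0.075) = 0.981/0.950.
- **D:** 85/8/7% and 65/30/5%, risks 1/0.6/1.8. B = (0.850 + 0.048 + 0.126)/(0.650 + 0.180 + 0.090) = 1.024/0.920.

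| Setting | B | True VE 0.40 reads | VE ratio | True VE 0.70 reads | VE ratio |
|---|---|---|---|---|---|
| A | 1.005 | 0.397 | 0.99 | 0.699 | 1.00 |
| B | 1.091 | 0.345 | 0.86 | 0.673 | 0.96 |
| C | 1.033 | 0.380 | 0.95 | 0.690 | 0.99 |
| D | 1.113 | 0.332 | 0.83 | 0.666 | 0.95 |

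**Reversal.** Swapping the two mixes inverts B. Setting D becomes 0.920/1.024 = 0.898, so a true VE of 0.40 reads 1 − 0.60 × 0.898 = 0.461, a ratio of 1.15.

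**Null cases.** If p1 = p0, or R = 1, given the other covariates, then B = 1 and there is no bias.

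The ratios apply to the affected group against the non-diseased. In a pooled diseased arm they are diluted if only one group is affected.

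**The case against.** **The coding may be settled elsewhere.** The indicator column of Table 2 points to Section 2.5.1, which sends the disease and sub-disease definitions to the online supplement. Exact coding is often left there or to a SAP. This stands in part. However, the article uses the three-group level consistently in the confounder description, both matching statements and the stratified analysis. Adding sub-disease terms would be a change to, or at least a clarification of, what it states.

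**Confounding is not shown.** This stands. Sub-disease confounds only if it predicts both vaccination and infection after exact matching on age, sex, place and disease group and adjustment for the rest. The article has no data on that. Without such imbalance, mixing sub-diseases is effect heterogeneity, which an ATT averages over, and not bias. Setting D is a strong assumption: axial spondyloarthritis at 8% against 30% despite matching on age, sex and place.

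**A stronger reading does not hold.** A reader might infer that the problem exists only in CIRD and IBD, has no counterpart in the non-diseased, and so passes undiminished into the VE ratio. The article does not support that. Section 2.5.1 takes in all MS subtypes, and Section 2.3 admits people with other chronic or life-threatening diseases, so the other groups are mixtures too. The net effect on the ratio has unknown size and direction.

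**Safeguards exist.** The urinary tract infection negative control (Section 2.6.6) may reveal residual confounding, and the article acknowledges that limitation. Detection does not remove it, though, and here a direct adjustment is available.

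**Matching on sub-disease would be costly.** This stands. It would thin the control pool against the 10% limit on unmatched vaccinated individuals, and Section 2.6.1 cites computational limits. This argues against changing the matching, not against adding model covariates.

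**Conclusion.** The point holds as a possible, inexpensively reduced source of residual confounding, not as a demonstrated bias. The sub-disease definitions have been applied to the data, disease enters matching and adjustment only as three groups, and no covariate shown restores the distinction.

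Under the assumed settings the relative risk is distorted by a factor of about 1.005 to 1.11. That is 0.3 to 6.8 percentage points on a true VE of 0.40 and 0.1 to 3.4 points on a true VE of 0.70. These figures precede any credit for the other covariates, so the remaining bias may well be smaller, and the direction cannot be stated in advance.

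Choosing disease groups as the level of the estimand is defensible. The point concerns only the covariates used to estimate it.

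**What to change.** 1. Add baseline indicators for rheumatoid arthritis, axial spondyloarthritis, lupus, Crohn's disease and ulcerative colitis to the Cox model used for g-computation. Because these nearly determine CIRD and IBD membership, either use one sub-disease per group as reference or let the indicators replace the group main effect. Keep the vaccination interaction at group level so that the estimand is unchanged.
2. Add the same indicators to the entropy-balancing weights in the weighted Kaplan-Meier sensitivity analysis, and carry them into the medication-stratified analysis for CIRD and IBD.
3. Report the balance of the five sub-diseases between vaccinated individuals and matched controls within CIRD and within IBD.
4. Leave the matching procedure unchanged.

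This fits Section 2.6.2, which already assigns confounders that are not matched to the Cox model. The cost is a few extra covariates. It needs no new data and loses no matches.
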